##### Experimental phase

The experimental phase (see Fig. 2) comprises the three previously described experimental conditions. During the experimental task, the participants will be wearing the devices described in the instruments section to measure electrophysiological signals. The experiment will be conducted in a controlled environment, which will be comfortable and noiseless, and where the temperature and humidity in the room will be controlled. The researcher will leave the room at the beginning of the experiment to avoid any possible conditioning.

**Fig. 2 Fig2:**
[figure not shown]
Experimental phase

At the start of the experiment, all the participants will be asked to complete the PANAS mood state scale [88]. This scale will be completed on three occasions: at the start of the task, following the negative mood induction (viewing the film clip) and after the autobiographical memory task (presentation of images according to the assigned experimental condition).

After completing the PANAS [88], the negative mood induction phase will begin. The participants will watch a 7-min section of the film “Dead Man Walking” (Polygram Filmed Entertainment, Havoc, Working Title Films), which shows the execution of a prisoner sentenced to death. Before seeing the film clip, the participants will be encouraged to experience the feelings generated by the clip as intensely as possible. After viewing the film clip, they will be asked to answer the control questions related to their level of concentration while watching the clip, and the degree to which they surrendered to the feelings it generated. They will then be asked to complete the PANAS [88] again in order to assess the effectiveness of the negative mood induction procedure.

Following the negative mood induction phase, the emotional recovery phase will be initiated, in which the participants will look at a total of six pictures previously selected according to their experimental condition in order to generate specific positive autobiographical memories. Each image will be presented for 1 min, and during this time, the participants will be asked to concentrate as hard as they can on the memory that each picture evokes with the aim of reliving the positive emotions they felt at that moment as intensely as possible. After each picture, the participants will answer a series of control questions related to their level of concentration while looking at the pictures and to what extent they were able to relive the emotions they felt at the moment related to the images. At the end of this phase, participants will once more complete the PANAS [88] in order to assess the effectiveness of the emotional recovery.

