## Objectives {7}

The ability to retrieve specific memories is a cognitive and emotional protective factor. Thus, developing and improving techniques that facilitate the generation of such memories, which are able to enhance mood state, could be highly effective in the prevention and/or reduction of depressive symptoms in healthy older adults. Consequently, the aim of the present study is to delve deeper into the knowledge and effectiveness of different visual stimuli in inducing positive emotions and reducing negative emotions, examining how the level of personal relevance of pictures as autobiographical memory cues may affect an individual’s emotion regulation. Importantly, this new knowledge could also be used in interventions focused on the training of specific positive memories with the aim of improving its efficacy in the treatment of clinical depression in the elderly population.

Additionally, given the differences in emotion regulation between young and older adults, we aim to assess whether the influence on emotion regulation of the level of personal relevance of the images differs according to a person’s age.

The main aim of this study, then, is to experimentally evaluate how the level of personal relevance of the images used as stimuli to access specific positive autobiographical memories can improve emotion regulation, especially in older adults. From this primary aim, we derive the following specific objectives:
To experimentally study the impact of the personal relevance of pictures on the improvement of mood state, following negative mood induction. To this end, we will use three types of images, classified according to their personal relevance: (a) personal autobiographical photographs (high personal relevance), (b) images of locations related to the participants’ lives (medium personal relevance) and (c) images from the IAPS (low personal relevance).Additionally, as suggested by Talarico et al. [82], events remembered with a high sense of reliving induce stronger emotions. For this reason, we will also examine the degree of reliving in the autobiographical memories evoked by the three types of images.To analyse any age-related differences in the effectiveness of the use of the three types of images to regulate emotion. We will compare the efficacy of the three categories of pictures (high, medium and low relevance) in inducing positive mood states in a group of young adults and a group of older adults.

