### Interventions

#### Explanation for the choice of comparators {6b}

The conditions of medium and high personal relevant images will be compared with IAPS images (low personal relevant condition). IAPS [41] is traditionally considered a valid system for affectively eliciting stimuli that can be used as a representative tool, for example, in mood and emotion induction studies. For this reason, its selection as comparator is justified.

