**Fig. 1 Fig1:**
[figure not shown]
Randomization phase

We will thus have three types of images varying in their level of personal relevance for each participant. The first type of images is pictures taken for the standardized IAPS. There will be a total of 40 pictures selected by the research team according to their level of positive valence (emotional valence values between 7.03 and 8.34). The participants will be asked to choose the 6 photos that best enable them to generate a specific positive autobiographical memory.

The second type of images used will be photos of locations and places that are significant for the participant, which will be selected following a prior interview in which the participant will be asked to name places that evoke specific positive autobiographical memories. These images will be taken from the Internet. We will select various images of each location, giving participants the opportunity to choose the one which best fits their memory.

The third type of images will be autobiographical photographs selected by participants from their own collection. Participants will be asked to previously select six photos, for which they can recall the exact moment they were taken and which are related to events that have made them feel happy during their lives. These six events will be those they are asked to recall in the experimental task.

For each of the memories retrieved in the three conditions, the following factors will be assessed: (1) the degree of nostalgia generated by the memory; (2) the intensity of the positive emotion evoked by the memory; (3) whether the participant was a spectator in the event (“as if I were watching a film”) or an actor (“as if I were seeing it with my own eyes or recording it”); (4) the significance of the event in the person’s life; (5) personal growth since the event occurred; (6) belief that the event has led them to better understand themselves and what life means; and (7) belief that they have learnt more about what life means as a result of the event.

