## Statistical methods

### Statistical methods for primary and secondary outcomes {20a}

#### Statistical analysis of the subjective variables

All analyses will be conducted using SPSS24.0 software. Firstly, ANOVAs and chi-square tests will be conducted to determine whether significant differences exist between the different intervention groups for the variables collected (PROMIS and PANAS scales) in the first assessment phase (Time 1) and for the level of immersion when viewing the film clip during the negative mood induction. If differences between groups are found in any of these variables, the variables with statistically significant differences will be included as covariate variables in the following ANOVAs. Secondly, to assess the impact of personal relevance of the images in emotional recovery, a repeated-measures ANOVA and post hoc Bonferroni tests will be performed in a mixed design with type of image (low, medium and high personal relevance groups) and group (young and older) as between-subjects variables and time (pre-test—Time 1—, post-negative emotional induction—Time 2—and post-positive emotional induction—Time 3) as within-subject variables. Finally, to assess the sense of reliving for the three groups of images, a repeated-measures ANOVA and post hoc Bonferroni tests will be performed in a mixed design with type of image (low, medium and high personal relevance groups) and group (young and older) as between-subjects variables and (average score of concentration level recalling the events and average score of the degree of reliving the positive emotions of the remembered events) as within-subject variables.

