## Discussion

The World Health Organization estimates that in 2050 there will be two billion people aged 65 years or older [99]. Population ageing, especially in developed countries, is an enormously important issue and is a challenge that heightens the need to create effective interventions to improve the mental health and quality of life of older persons. These predicted figures for population ageing also suggest there will be greater demand for effective alternative preventive treatments for depression, taking into account its prevalence in older adults [100, 101].

Emotion regulation is a key factor in adaptive functioning throughout life, being associated with cognitive, physical and social health [102]. This study protocol describes the design of a randomized controlled trial that aims to analyse how effective different types of autobiographical stimuli are in inducing positive emotions, analysing the variables that might enhance individuals’ emotion regulation for their use in the prevention of depressive symptoms.

The findings of this study will enhance knowledge of the functioning of positive mood induction procedures, which will help to better understand the processes involved in emotions in ageing and to assess the effect of ageing on emotional response and regulation and thus, also on older adults’ well-being. In addition, the results will lay the foundations for the development of future interventions designed to facilitate emotion regulation in both young and older adults, but above all in the latter, adapting the different techniques to the age group to ensure they are as effective as possible. In this sense, the knowledge derived from this study might allow individuals to use preventive techniques in their daily life and in their own homes, and thus the applicability of the findings will be considerable.

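### The comparison of image types is sound, but with positive recall in every arm the mood change after the film cannot support the protocol's wording that the images are effective in absolute terms

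*Protocol article*

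**What the plan says.** **Task.** After the film, participants in every condition "look at a total of six pictures previously selected according to their experimental condition in order to generate specific positive autobiographical memories", all under the same request to relive the positive emotion (Experimental phase). "Each image will be presented for 1 min", with control questions after each one.

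**Comparator.** "The conditions of medium and high personal relevant images will be compared with IAPS images (low personal relevant condition") (Explanation for the choice of comparators {6b}). The IAPS arm is itself a recall arm. From 40 pictures preselected for positive valence, "The participants will be asked to choose the 6 photos that best enable them to generate a specific positive autobiographical memory" (Pre-experimental phase). No arm waits, views neutral pictures or recalls neutral events.

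**Measurement and analysis.** PANAS is completed before the film (Time 1), after it (Time 2) and after the pictures (Time 3). Of the last one the protocol says: "At the end of this phase, participants will once more complete the PANAS [88] in order to assess the effectiveness of the emotional recovery". The analysis section states that "to assess the impact of personal relevance of the images in emotional recovery, a repeated-measures ANOVA and post hoc Bonferroni tests will be performed", with image type and age group between subjects and the three times within subjects.

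**Aims and conclusions.** The Objectives {7} speak of the "effectiveness of different visual stimuli in inducing positive emotions and reducing negative emotions", and the closing Discussion says the trial "aims to analyse how effective different types of autobiographical stimuli are in inducing positive emotions". The Abstract's discussion suggests that such images could be a means of producing positive mood, with implications for treating depression.

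**The concern.** Mood lowered by a 7-minute clip may rise again once the clip is over, whatever is shown next. Participants also answer the PANAS for the third time, know what they were given (Who will be blinded {17a}) and have been asked to relive positive feelings. All of this enters the change from Time 2 to Time 3 in each arm.

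The protocol uses the word effectiveness in two senses. One is relative: does higher personal relevance do better than IAPS pictures? The other is absolute: do these images induce positive emotion and reduce negative emotion? The arms can answer the first but not the second. The analysis section includes time and post hoc tests without saying which result carries the effectiveness claim. A rise in all arms could therefore be read as showing that all the image types work.

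**Working it through.** **What each contrast estimates.** Write the expected Time 2 to Time 3 change in arm j and age group a as

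change(j, a) = s(a) + q(a) + c(j, a)

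where s is recovery because the film has ended, q is the effect of repeated testing and of the common reliving instruction, and c is the cue effect. The terms are taken as additive.

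- Within one arm: s + q + c. The cue effect is not separated.
- Time main effect: s + q + the average c. The same problem.
- High versus IAPS: (s + q + c_high) − (s + q + c_IAPS) = c_high − c_IAPS. The shared terms cancel by randomisation.
- Age by time: the difference between age groups in s + q + average c. Age is not randomised, so a different natural recovery rate is not excluded.
- Image type by age by time: s(a) and q(a) cancel within each age group before the groups are compared, leaving the difference in c_high − c_IAPS.

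c_IAPS is never estimated by itself, because no arm estimates s + q alone.

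**Time available.** Six images of 1 minute give at least 6 minutes between Time 2 and Time 3. The timeline table allows about 25 minutes for the whole task; 25 − 7 = 18 minutes is a rough ceiling, since that row may also include the film control questions.

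**Size.** The protocol states no figure for spontaneous recovery, so there is nothing to reproduce. Two illustrations follow, both resting on assumptions.

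*Decay.* Share of the induced drop gone after t minutes with half-life h: 1 − 2^(−t/h), assuming exponential decay.

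| h (assumed) | t = 6 min | t = 18 min |
|---|---|---|
| 5 min | 56% | 92% |
| 10 min | 34% | 71% |
| 20 min | 19% | 46% |

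The range, 19% to 92%, shows only that the amount is unknown and need not be small.

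*Significance with no cue effect.* Take 40 + 40 = 80 per arm, c = 0 everywhere, spontaneous recovery of d SD and a Time 2–Time 3 correlation r. The paired t test has noncentrality d/√(2(1 − r)) × √80. For d = 0.3 and r = 0.5 this is 0.3 × 8.944 = 2.68. Tests are two-sided at 5%, without Bonferroni correction; corrected tests would reject somewhat less often. The last two columns come from 3,000 simulated trials per setting.

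| d | r | One arm significant | All three significant | Image type by time significant |
|---|---|---|---|---|
| 0.2 | 0.5 | 42% | not simulated | not simulated |
| 0.3 | 0.5 | 76% | 44% | 4.9% |
| 0.5 | 0.5 | 99% | 98% | 5.1% |
| 0.2 | 0.8 | 80% | not simulated | not simulated |
| 0.3 | 0.8 | 99% | 96% | 5.0% |
| 0.5 | 0.8 | 100% | 100% | 5.3% |

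As a check, the arms are independent, so all three should be significant with the cube of the single-arm probability: 0.755³ = 0.43 and 0.993³ = 0.98, in line with the simulation.

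The between-arm test keeps its 5% level. The within-arm reading does not distinguish useless cues from useful ones.

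**The case against.** The strongest reply is that the plan is comparative. The main aim concerns the level of personal relevance, Trial design {8} compares three types of stimuli, {6b} names a comparator, and Dissemination plans {31a} describe the primary papers in terms of levels of relevance. The stated purpose of the ANOVA is the impact of personal relevance, which image type by time answers. All of this stands.

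A reader might infer that the plan takes the time main effect, or a within-arm test, as its criterion of effectiveness, or an age-by-time difference as evidence of picture efficacy. No section says so. A reader might also infer that a large time effect with small arm differences is the likely result and would be reported as success for all three image types. The documents contain no such forecast or reporting rule; the sample size section assumes a medium effect.

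Nor should the point be stretched to say that the trial can show no benefit of any cue. High relevance beating IAPS would be a randomised difference that shared recovery and the shared instruction cannot explain. Unless IAPS-cued recall worsens mood, it would show a real benefit. Positive affect above its pre-film level would also exceed a simple return to baseline, though it would remain an uncontrolled before–after change.

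The sentence on the final PANAS may do no more than mirror the earlier check of the negative induction, and the Abstract is hedged. But hedging does not supply a reference condition, and the Objectives and Discussion still state the absolute aim. This is therefore not a detail left to an analysis plan: the article itself words an inference that its arms cannot support.

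**Conclusion.** The point holds in a limited form. The randomised comparison of image types is sound and answers the main aim, overall and by age group. The absolute statements in the Objectives, Experimental phase, Discussion and Abstract have no concurrent reference, because every arm performs positive recall. The within-arm Time 2 to Time 3 change, the time main effect and age by time cannot carry them.

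This conclusion rests on the arms as described and on additivity of shared and cue effects. It does not depend on the illustrative figures, whose half-lives, recovery sizes and correlations are all assumed. How much mood would recover unaided in this trial cannot be known from the documents.

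**What to change.** 1. In the analysis of the subjective variables, state that effectiveness is judged by the between-arm contrasts, high versus IAPS and medium versus IAPS, overall and by age group. Choose in advance either the Time 2 to Time 3 change or Time 3 adjusted for Times 1 and 2. Unadjusted Time 3 alone would discard information that the planned model uses.
2. State there that the time main effect, the within-arm Time 2 to Time 3 post hoc tests and age by time are descriptive, because recovery after the film is not separated from the cue effect. Keep image type by age by time as the test of the age question.
3. In the Objectives, Experimental phase, Discussion and Abstract, word aims and conclusions as more, or not more, effective than IAPS-cued recall.

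This needs no new arm, participants or procedures. The cost is that the claim of absolute effectiveness is given up. Keeping that claim would require a concurrent neutral or no-recall condition; at the present arm size that means 40 + 40 = 80 more participants (240 to 320), a much larger change.

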#### Criteria for discontinuing or modifying allocated interventions {11b}

Not applicable. The interventions will not be modified. Participants may leave the trial at any time if they wish. Participants who do not complete the entire trial will be excluded from the study.

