### Participant timeline {13}

Participant recruitment is expected to begin in October 2020 and continue for 2 months. Nevertheless, if the minimum number of participants in each experimental group is not reached in early December, the recruitment period will be extended until the required minimum is reached. In this phase, those who agree to participate will complete the screening questionnaires.

The pre-experimental and experimental phases will take place 7–21 days after randomization. Both phases will take place on the same day. In the pre-experimental phase, participants will select the images to be displayed in the experimental task according to the group to which they are assigned (low, medium or high personal relevance). Finally, in the experimental phase, they will complete the mood questionnaires and the experimental task.

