### Recruitment {15}

People interested in participating in this study will be provided with a detailed information sheet supplemented with a verbal explanation of the study procedure. If the participants agree with this information, the screening questionnaires will be completed. The research psychologists will obtain the informed written consent of each participant prior to the screening phase. The questionnaires in this phase will include a complete sociodemographic history, a screening test to assess the presence of cognitive impairment and scales to measure anxiety and depression symptoms. Of these individuals, all participants meeting the inclusion criteria will be recruited for the study. Recruitment will continue until the minimum number of participants in each group is reached.

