#### Implementation {16c}

All patients who give consent for participation and meet the inclusion criteria will be randomized.

The random assignment of participants will be conducted by a member of the Psychology Department blinded to the objectives of the study. This staff member will send a third research psychologist a list with the random assignation of each participant to each intervention group. This psychologist will not be involved in the recruitment of participants or in assessing the outcomes of the study. The psychologists responsible for participant recruitment will not be allowed to receive information about group allocation.

Throughout the study, the randomization will be conducted by the same member of the Psychology Department in order to keep the data management and the statistician blind to the study condition. Thus, randomization will be conducted without any influence from the researchers involved in the study.

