### Methods in analysis to handle protocol non-adherence and any statistical methods to handle missing data {20c}

Missing data (essentially, unanswered items from the screening measures) will be handled using a multiple imputation approach. This approach is based on the creation of a set of imputations for the respective variables with missing data. To this end, we will use a set of repeated imputations created by predictive models based on the majority of participants with complete data. After the imputations are completed, all of the data (complete and imputed) will be combined and the analysis performed for each imputed and completed dataset. Rubin’s method of multiple imputation will be used to estimate effects. We propose to use 100 datasets.

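### Randomised participants who do not complete are excluded and the planned imputation is aimed at screening items, so the arm comparison is a completer analysis with a possible bias of unknown direction and size

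*Protocol article*

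**What the plan says.** The protocol article, section {11b}, says "Participants may leave the trial at any time if they wish" and continues: "Participants who do not complete the entire trial will be excluded from the study". No analysis set is named that would limit this to participation rather than analysis.

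On timing, section {16c} states "All patients who give consent for participation and meet the inclusion criteria will be randomized", and section {13} states "The pre-experimental and experimental phases will take place 7–21 days after randomization".

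On missing data, section {20c} states "Missing data (essentially, unanswered items from the screening measures) will be handled using a multiple imputation approach", with 100 datasets combined by Rubin's method. Its title covers non-adherence, but its text gives no rule for it.

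The subjective-outcome analysis in {20a} is a repeated-measures ANOVA in SPSS over three PANAS times, with image type and age group as between-subjects factors. Retention measures ({18b}) are declared not applicable because there is a single session. Section {15} adds: "Recruitment will continue until the minimum number of participants in each group is reached".

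**The concern.** Randomisation makes the three arms comparable at allocation. Removing people afterwards keeps that comparability only if the removal is unrelated to arm or unrelated to outcome. The plan gives no reason to take either for granted.

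- **Tasks differ by arm** (intervention description). The low-relevance arm picks 6 of 40 supplied pictures. The medium-relevance arm names meaningful places in an interview. For the high-relevance arm, "Participants will be asked to previously select six photos, for which they can recall the exact moment they were taken".
- **Participants are not blinded** ({17a}).
- **The session includes a distressing film clip**, and {30} and {22} foresee that the recovery task may not work for some. Someone who stops during the picture task because it does not help carries information about the assigned condition, and the rule deletes that person.
- **Recruiting until group minimums are met** could restore the numbers but not the randomised comparison.

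The trial's main conclusion, the effect of personal relevance on emotional recovery, is a between-arm comparison and so depends directly on this rule.

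**Working it through.** **Step 1: does the rule act after randomisation?** The order is consent and screening, randomisation of all who are eligible ({16c}), a wait of 7 to 21 days, then image selection and the experiment on one day ({13}). Whether someone completes the trial is known only at the end of that chain, so the rule necessarily reaches randomised participants.

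**Step 2: does the imputation repair it?** No. Imputing screening items fills in questionnaires completed before allocation. It supplies no outcome for a person who has been taken out. SPSS repeated-measures ANOVA also uses only cases with all three times present, so a participant missing one PANAS drops out unless that value is filled in.

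**Step 3: size.** The article gives no non-completion rate and no figure for bias, so there is nothing to reproduce. The one usable planning figure is the effect size in {14}, a partial eta squared of 0.06.

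*Planned effect on an SD scale.* f = sqrt(0.06 / 0.94) = 0.2526. For three equally spaced arm means (-a, 0, a), f = a × sqrt(2/3), so a = 0.2526 × sqrt(1.5) = 0.309. The high-low gap is 2a = 0.62 SD. Equal spacing is my assumption.

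*Bias in a completer comparison.* Suppose a share d of an arm is lost and completers exceed non-completers by g SD. The completer mean then exceeds the full-arm mean by d × g. With the same g in both arms, the bias in their difference is (d1 - d2) × g. All values of d and g are assumptions.

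| Loss in the two arms | g = 0.25 | g = 0.5 | g = 1.0 |
|---|---|---|---|
| 10% vs 5% | 0.0125 | 0.025 | 0.05 |
| 20% vs 5% | 0.0375 | 0.075 | 0.15 |

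As a share of 0.62 SD, the first row is about 2% to 8% and the second about 6% to 24%.

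The table is a range, not a bound. If g differs between arms, the bias is d1 × g1 - d2 × g2. For example, 0.20 × 1.0 - 0.05 × 0.25 = 0.19 SD.

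*Near worst case.* One arm loses exactly its worst share p on a normal outcome and the others lose no one selectively. The arm mean rises by phi(z_p) / (1 - p), which is 0.11, 0.20 and 0.35 SD for p = 5%, 10% and 20%. At 10% the implied g is 0.195 / 0.10 = 1.95 SD, well outside the table.

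**Step 4: numbers.** If 240 completers are wanted, replacement means randomising 240 / 0.95 = 253 at 5% loss, 240 / 0.90 = 267 at 10%, or 240 / 0.80 = 300 at 20%. That deals with precision only. The bias in Step 3 does not shrink as N grows.

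**The case against.** The other side has several good points.

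- **Loss may be small.** The study calls itself exploratory, enrols healthy volunteers, runs both phases on one day and collects the PANAS by computer within the session. This stands, and it limits the likely size. It does not cover non-attendance during the 7 to 21 days.
- **Those lost while waiting cannot have left because of a session outcome they never had.** This stands. Section {13} also places image selection on the session day, so part of this loss may be unrelated to arm. What remains is loss through traits that affect both the arm's preparation and later mood.
- **Selection on a stable mood level largely cancels.** It would shift Time 1 as well as Time 3 and mostly drop out of the image type by time interaction. This stands for stable level, but not for selection on responsiveness to the pictures.
- **The imputation text says essentially, not only, and a fuller plan may treat missing outcomes.** This is fair, so silence on outcome imputation is not the point. The exclusion sentence is explicit, and people excluded under it stay absent whatever is imputed.

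A reader might infer that the bias favours the high-relevance arm, because that arm would be selected for people rich in retrievable memories. The documents do not support this. Every arm has to find images that evoke specific positive memories, the schedule gives one 25-minute selection step for all arms, and stock pictures could prove as hard to match to a memory as one's own album.

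A reader might also infer that imputing screening items leaves eligibility uncertain from one imputed dataset to the next. Section {16b} rules this out: criteria are verified before the allocation code is released.

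**Conclusion.** The point holds. The article fixes a post-randomisation exclusion, and its imputation plan does not offset it. The between-arm ANOVA is therefore a completer analysis, open to bias if loss is related to both arm and outcome.

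Direction and size are unknown. Under the assumed loss rates and a common completer/non-completer gap, the bias is about 0.01 to 0.15 SD against a planned high-low gap of about 0.62 SD. The 0.20 SD figure, roughly a third of that gap, needs perfectly selective loss of 10% in one arm and should be read as a near worst case, not an expectation. That loss depends on arm is an inference from the differing tasks and the lack of blinding; no arm-specific rate is stated.

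In a single-session exploratory study this does not invalidate the design. It is a defect worth correcting before outcomes are examined, because data not kept from non-completers cannot be recovered.

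**What to change.** 1. Replace the exclusion sentence in {11b} with: all randomised participants are analysed in their allocated arm, and data collected before withdrawal are kept.
2. In {20c}, extend the planned 100-dataset imputation to the PANAS outcomes, using arm, age group, PROMIS, demographics and any available PANAS. Alternatively, replace the ANOVA with a likelihood mixed model over Times 1 to 3.
3. Report the numbers randomised, attending and completing in each arm, with reasons for loss.
4. Keep the completer analysis as a sensitivity analysis.
5. State that the methods in item 2 assume data are missing at random and add little for people who never attend. Accompany them with a simple sensitivity analysis that gives non-completers less favourable values, for example imputed values worsened by 0.25 to 1.0 SD, the same assumed range as above.

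The cost is wording in two sections, probably through the formal amendment route in {25}, plus a modest amount of extra analysis and record-keeping. No additional participants are required.
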